#### Aim 1: Compare the effectiveness of two implementation strategies, alone and in combination, to improve use of interpretation and comprehension for patients/parents with language barriers seen in adult/pediatric primary care settings

We hypothesize that, compared to educational modules, provider access to mobile video interpreting will lead to (*H1*) greater odds of interpreter use for visits with patients/parents with language barriers (primary outcome) and (*H2*) better comprehension among patients/parents with language barriers. We also hypothesize (*H3*) that mobile video interpreting and educational modules together will yield greater odds of interpreter use than either strategy alone.

To test *H1* and *H3*, we will use assigned strategy and data collected during phases 1 and 2. Under the SMART design, comparisons of first-stage interventions, comparisons of second-stage interventions, and comparisons of the adaptive intervention with both stages can be conducted simultaneously using standard software with a technique called a “weighted and replicated” regression approach, using weighted generalized estimating equations (GEE) [66, 97]. Weighted GEE allows us to work with binary outcomes and weights and adjust for clustering within providers. Within-clinic correlations will be assessed by including clinic-specific random effects in our regression models and estimating the intra-cluster correlation coefficients. Significance of the intra-cluster correlation coefficients will be examined by comparing models with and without clinic-specific random effects using likelihood ratio tests. If no strong within-clinic correlation is detected, we will use fixed-effects regression models for their better power; otherwise, estimates and inference based on random-effects regression models will be reported. *H1* and *H3* will be tested using the Wald test and robust standard error estimates [66, 97]. Model-based estimates of odds ratio comparing education to mobile video interpreting or both will be reported, along with 95% confidence intervals [98].

To test *H2*, our analytic sample will include only patients who completed a post-visit survey (*n* = 648). A weighted GEE logistic regression model predicting patient/parent comprehension at the visit level will be estimated. Baseline covariates will include the clinic, patient demographics (age, sex, language), and patient comorbid conditions [99–102], pooled at the provider level. Model-based estimates of the odds ratio comparing education to mobile video interpreting or both will be reported, along with 95% confidence intervals computed via parametric bootstrapping [98].

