### Study design and randomization

This type 3 hybrid implementation-effectiveness study will test two discrete implementation strategies for improving professional interpreter use (primary implementation outcome) and patient comprehension (secondary effectiveness outcome) in primary care. The implementation strategies—interactive web-based educational modules and access to mobile video interpreting—target different sets of barriers to professional interpreter use, an evidence-based practice [20, 21, 34, 82, 83]. Our results will therefore provide insights into how best to promote implementation of a well-studied, well-established practice known to improve outcomes but inconsistently used. As the potency of barriers may vary by provider and clinic, we will test the strategies alone and in combination, using a SMART design, with provider-level randomization.

A total of 55 providers from 3 to 5 primary care clinical organizations will be randomized 1:1 to either education or mobile video interpreting access, stratified by baseline interpreter use and clinic (phase 1; Fig. 2). Randomization will occur within REDCap, using a sequence generated by the study biostatistician and implemented by a research coordinator. After 9 months, providers with interpreter use in the top tertile (within strategy) will remain with the original strategy; those in the bottom two tertiles will be randomized 1:1 again, to continue the original strategy or to add the second strategy to the first (phase 2). After another 9 months of data collection, we will provide free access to both mobile video interpreting and educational modules to all enrolled providers and then track voluntary uptake by those not previously exposed for another 9 months (phase 3). Data collection will include *administrative data* to track interpreter use (primary outcome); *patient surveys and qualitative interviews* to determine diagnosis comprehension (secondary outcome) and communication quality; *provider surveys and qualitative interviews* to assess contextual and intrapersonal barriers and moderators; and *visit video recording* to capture additional barriers and determine fidelity of strategy implementation. We will assess each strategy’s effectiveness, alone and in combination, for improving professional interpreter use and patient comprehension. We will explore mechanisms by which these strategies work and evaluate the relative strategy-specific costs.

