**Fig. 2 Fig2:**
[figure not shown]
SMART design depicting 2 rounds of provider randomization over 18 months with active data collection and 9 months of follow-up

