#### Interpreter use

Interpreter vendor invoices will be collected from companies that clinics currently contract with; mobile video interpreting invoices will be managed by the study team. All professional interpreter invoices (not just mobile video interpreting) will be matched to clinic visits for patients who use a language other than English (all languages) for enrolled providers. We will calculate baseline interpreter use for enrolled providers for the six months pre-randomization and then randomize 1:1 to education or mobile video interpreting, stratified by baseline use and clinic. We will calculate interpreter use, both overall and strategy consistent, continuously throughout phases 1–3; other data collection will end after phase 2.

For analysis, interpreter use will be defined as a dichotomous variable at the level of the clinic visit. Visits with patients who use a language other than English with any billed professional interpreter use will be coded as “yes,” and the remainder will be coded as “no.”

Sample size calculations consider aim 1 group comparisons (mobile video interpreting, education, combination) at the end of phase 2. We assume loss of up to 9 providers (e.g., to job change; 16%) over the study; we expect attrition (up to 27%) in provider interviews and surveys, but that will not impact aim 1 power. With 5796 total encounters with patients who use a language other than English (7 visits/provider/month), we expect 1932 non-English visits per group, which will provide > 80% power to detect a 5% difference in proportion of professionally interpreted visits by groups [46, 57]. This will be readily feasible with administrative data.

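### H3 is not tied to one SMART contrast, and the stated data window, three-level odds ratio and group sizes do not fit a combination given only in phase 2 to lower-use providers

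*Protocol article*

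**What the plan says.** Under Study design and randomization, providers "will be randomized 1:1 to either education or mobile video interpreting access". After 9 months, "providers with interpreter use in the top tertile (within strategy) will remain with the original strategy", while "those in the bottom two tertiles will be randomized 1:1 again", either to continue or to add the other strategy. Phase 2 lasts a further 9 months.

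Under Data analysis, Aim 1, H3 states that "mobile video interpreting and educational modules together will yield greater odds of interpreter use than either strategy alone". For H1 and H3, "we will use assigned strategy and data collected during phases 1 and 2". The method is a weighted and replicated GEE. The section notes that this method can compare first-stage interventions, second-stage interventions and whole adaptive interventions, but it does not say which of these tests H3. The result to be reported is "Model-based estimates of odds ratio comparing education to mobile video interpreting or both will be reported".

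The sample-size paragraph under Interpreter use considers "group comparisons (mobile video interpreting, education, combination) at the end of phase 2". It counts 5796 visits, 1932 per group, with more than 80% power for a 5-point difference.

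**The concern.** A top-tertile provider never receives the combination in phases 1 and 2, and no provider receives it in phase 1. A data set covering both phases, split into education, mobile video interpreting and both, therefore does not hold three randomized groups. The combination group is selected for low earlier use, and the single-strategy groups contain every high user.

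The SMART weights remove that selection, but the contrast they then give is between adaptive interventions. Most of the data in such a contrast are the same on both sides.

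An analyst following the text could thus report a combination odds ratio that is pulled downwards by selection, or one that is valid but much smaller than the effect H3 describes, and could label either one as the effect of both strategies. The same three-way structure returns in the H2 analysis and in Aim 3, which takes its effectiveness measures from Aim 1.

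**Working it through.** **Inputs from the article:** 55 providers less 9 lost = 46; 7 visits per provider per month; two 9-month phases; 1:1 allocation at both randomizations; top third not re-randomized. **Assumed, because not stated:** two-sided alpha 0.05, mean interpreter use 50% unless a range is shown, provider intraclass correlation (ICC) 0.05 to 0.20 unless stated.

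**1. The plan's own figure.** 46 x 7 x 18 = 5796 and 5796 / 3 = 1932, as stated. With independent visits, 1932 per group and 50% against 55%: SE = sqrt((0.25 + 0.2475) / 1932) = 0.0160; 0.05 / 0.0160 = 3.12; 3.12 - 1.96 = 1.16; power 0.876. For base rates from 20% to 80%, power is 0.875 to 0.984. The stated power therefore reproduces, but only for three equal groups with independent visits over 18 months.

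**2. Visits made under the combination.** 46 x 2/3 x 1/2 = 15.3 providers, each with 7 x 9 = 63 phase 2 visits, gives 966. The figure of 1932 is reached only by also counting the same providers' phase 1 visits, before the combination started (15.3 x 126 = 1932). By strategy in force over 18 months the split is 966 combination visits and (5796 - 966) / 2 = 2415 for each single strategy.

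**3. Share of an adaptive intervention that can differ.** Top-tertile providers (1/3) count on both sides, and phase 1 (half the time) precedes the second randomization. So 2/3 x 1/2 = 1/3 of the weighted data can differ, and 5 points x 1/3 = 1.67 points.

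**4. Simulation** (46 providers, 63 visits per phase, tertile rule applied within arm; weights 2 for top-tertile and 4 for re-randomized providers). Entries are combination minus comparator, in percentage points; triples are for ICC 0.05 / 0.10 / 0.20.

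| Contrast | No true effect | True effect of 5 points |
|---|---|---|
| Unweighted, providers grouped by final assignment, 18 months | -9 / -13 / -19 | not run |
| Unweighted, phase 2 only | -8 / -12 / -18 | -3.0 / -7.2 / -13.3 |
| Unweighted, by strategy in force at the visit, 18 months | -6.4 / -9.8 / -14.6 | -1.4 / -4.8 / -9.7 |
| Weighted adaptive interventions, phases 1 and 2 | within 0.1 of zero | 1.6 to 1.7 |
| Weighted adaptive interventions, phase 2 only | within 0.1 of zero | 3.2 to 3.4 |
| Second stage: add vs continue, re-randomized providers, phase 2 | within about 0.1 of zero | 4.9 to 5.2 |

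At ICC 0.02 the by-visit unweighted bias is still -3.4 points.

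**5. Does pooling lose power?** For a 9 to 10 point effect (0.4 on the logit scale) at the same three ICCs, with both models adjusted for phase 1 use, power is 88% / 86% / 78% for the pooled adaptive-intervention contrast and 87% / 83% / 77% for the second-stage contrast. The estimate and its standard error shrink together.

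**6. Power at the actual group size.** For 966 against 966 independent visits and 5 points, power is 0.65, 0.60 and 0.69 at base rates of 30%, 50% and 70%. Within one first-stage strategy (483 against 483) it is 0.38, 0.34 and 0.41. Unadjusted provider clustering would lower these further; that is a separate matter.

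**The case against.** The strongest reply is that the plan is not forced into a bad contrast. Aim 1 names second-stage comparisons among those its method can make. It specifies weighting that removes the selection, and the primary analyses are by intention to treat. The window of phases 1 and 2 may simply be the data source for H1 and H3 jointly. The article is condensed, and an analysis plan may settle the rest.

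Much of this stands, and it rules out three stronger readings:

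- *That the H3 analysis must be either confounded or diluted.* The second-stage contrast on phase 2 visits is neither, and the article names that kind of comparison. The confounded version arises only if the three groups are compared without the planned weights.
- *That pooling both phases throws away most of the power for H3.* An unadjusted model does suggest this (23% / 13% / 6% pooled against 65% / 46% / 26% second stage). However, the unadjusted pooled test is very conservative, with a null rejection rate of 1.5% / 1.4% / 1.2%. With the same adjustment for phase 1 use, the difference disappears.
- *That H1 should be tested on phase 1 alone.* A first-stage effect averaged over second-stage options is a recognised SMART estimand. Pooling shrinks a constant difference only to (1 + 2/3) / 2 = 5/6, and phase 1 includes the months when booster modules are still being released. This is a trade-off and not an error.

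The reply does not remove the point. The article does not leave the matter open: it states a data window, a three-level odds ratio and group sizes, and these do not match the second-stage contrast. Saying that a comparison can be made does not assign it to H3.

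**Conclusion.** The point holds in this form: H3 is not tied to a contrast, and the details that are stated point away from the one that answers it directly. The 1/3 factor and the 966 visits follow from the design by arithmetic, taking exact tertiles and the planned 46 providers and visit rate. The downward bias of an unweighted three-group comparison follows from the tertile rule whenever providers differ in their underlying use. Its size, roughly 6 to 19 points, depends on the assumed 50% mean use, an ICC of 0.05 to 0.20, and how visits are assigned to groups. Over that range it exceeds the 5-point difference the trial is sized to detect. For the weighted contrast over both phases the fault is one of meaning: a 5-point effect of the combination is reported as about 1.7 points. This should be settled before analysis, because it concerns a named hypothesis on the primary outcome.

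**What to change.** - In Aim 1, name the test of H3 as the randomized second-stage contrast: add versus continue among re-randomized providers, phase 2 visits only, adjusted for first-stage strategy, phase 1 use and clinic.
- Report the weighted and replicated contrasts of adaptive interventions separately and label them as such. Present no odds ratio of both against education as the effect of the combination unless it is one of these two. Carry the same definition into H2 and the Aim 3 denominators.
- In the sample-size paragraph, replace 1932 combination visits by about 966 against 966, and restate the power.

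The cost is wording and a recalculation; no change to conduct or data collection is needed. There are two real downsides. H3 then applies only to providers outside the top tertile, the only ones randomized to the combination. The stated power also becomes less favourable: about 0.60 to 0.69 for 5 points with independent visits and no covariate adjustment, and lower if H3 is examined within each first-stage strategy.

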#### Patient/parent comprehension

Patient comprehension will be determined by asking surveyed patients (*n* = 648) to report the diagnosis they received during their visit with an enrolled provider. The parent-reported diagnosis will then be compared to the provider-documented diagnosis, which trained abstractors will have abstracted from the EMR. Two coders blinded to study assignment will compare the documented diagnosis to the patient-reported diagnosis to determine comprehension, coded as yes, concordant; no, not concordant; or unclear, based on the standard of whether a different follow-up provider would likely know the diagnosis based on the information provided by the patient. For analysis, comprehension will be coded as yes or no/unclear. We have successfully used these procedures previously [46].

In addition to measuring comprehension, the survey will use validated measures to collect demographics and satisfaction with communication and interpretation. The tablet-based survey will have an audio feature to allow patients to read or hear the questions in 4 non-English languages. The survey will be completed in the clinic whenever possible; otherwise, the patient will complete it within 7 days, independently online or over the telephone with a bilingual research coordinator or professional interpreter.

Based on aim 1 analyses, with 216 completed patient surveys per group (648 total), we will have ≥ *80% power to detect a 14% difference in diagnosis comprehension by group* [46]. This will also be feasible, achieved by surveying 7–12 patients per clinic per month for 18 months.

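### The primary interpreter-use model should not be picked by a likelihood ratio test on about 3–5 clinics; fix one weighted GEE that adjusts for both randomization strata

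*Protocol article*

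**What the plan says.** The Protocol article, Data analysis, Aim 1, tests H1 and H3 by weighted and replicated regression: a weighted GEE with clustering on provider, Wald tests and robust standard errors. The same paragraph adds clinic random effects and judges them by "comparing models with and without clinic-specific random effects using likelihood ratio tests". The outcome of that test sets the reported model: "If no strong within-clinic correlation is detected, we will use fixed-effects regression models for their better power"; otherwise a random-effects model is reported.

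Under Study design and randomization, providers are randomized "stratified by baseline interpreter use and clinic". The Interpreter use section makes the second stratum available for everyone: "We will calculate baseline interpreter use for enrolled providers for the six months pre-randomization". The H2 paragraph names clinic among its covariates. The H1/H3 paragraph names no covariate.

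**The concern.** The primary analysis has two possible forms, and the trial's own data choose between them by a rule that is not fully fixed. There is no threshold for a strong correlation, and the number of clinics is too small for a clinic variance to be estimated well.

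The test also sits outside the planned inference. A GEE has no likelihood, so a likelihood ratio test must come from some other model, and the text does not say which. In particular, it does not say whether that model has a term for provider variation.

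The reason given for the switch is power. Yet clinic is a randomization stratum, and leaving a prognostic stratum out of the analysis normally widens the standard error. At stake are the precision of the primary comparison, with about 46 providers expected to remain, and a model form that depends on noise.

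**Working it through.** **Inputs from the Protocol article**
- "A total of 55 providers from 3 to 5 primary care clinical organizations will be randomized 1:1" (Study design and randomization).
- "We assume loss of up to 9 providers" (Interpreter use): 55 − 9 = 46 providers.
- Visits: 46 × 7 per month × 18 months = 5796, which matches "5796 total encounters with patients who use a language other than English". Divided by 3 groups this is 1932, as stated.
- Number of clinics: the article gives 3–5 organizations. The Patient/parent comprehension section plans "surveying 7–12 patients per clinic per month for 18 months". For 648 surveys, 648/18 = 36 per month; 36/12 = 3.0 and 36/7 = 5.1. So about 3–5 clinics.

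**The plan's own power figure.** The article gives no base rate. The worst case is near 50%, for example 0.475 vs 0.525. The SE is √(2 × 0.475 × 0.525 / 1932) = 0.0161, so z = 0.05/0.0161 − 1.96 = 1.15 and power is 0.875. The claim of more than 80% reproduces, with visits treated as independent. It carries no information about provider or clinic variation.

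**Assumptions for the checks below.** The article gives no variances or correlations. Assumed on the logit scale: provider variance 0.3, clinic variance 0 to 0.37, log odds ratio 0.3, baseline-to-follow-up correlation 0.7 (varied from 0.4 to 0.85). The simulations use 46 providers and stratified randomization. They cover the first-stage two-arm comparison with 63 visits per provider (7 × 9), not the full weighted-and-replicated analysis.

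**Step 1. How often the test detects clinic variation when provider variation is allowed for** (5% level, boundary mixture). Latent ICC = clinic variance / (clinic variance + 3.29).

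| Clinic variance | Latent ICC | 3 clinics | 4 clinics | 5 clinics |
|---|---|---|---|---|
| 0 | 0 | 2% | 3% | 3% |
| 0.05 | 1.5% | 18% | 23% | 23% |
| 0.10 | 2.9% | 38% | 39% | 46% |
| 0.17 | 4.9% | 56% | 60% | 63% |
| 0.37 | 10.1% | 76% | 84% | 84% |

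**Step 2. The same test with no provider term, true clinic variance zero** (126 visits per provider). It rejects in 63%, 75% and 87% of trials with 3, 4 and 5 clinics. The arithmetic shows why. With 46/4 = 11.5 providers per clinic, provider variation contributes 0.3/11.5 = 0.026 to the variance of a clinic mean. Binomial sampling at 50% contributes only 4/(11.5 × 126) = 0.0028. The test attributes the excess, about nine times the sampling variance, to clinic.

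**Step 3. Effect on the standard error of the log odds ratio** (4 clinics, correlation 0.7, mean SE).

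| Clinic variance | Neither stratum | Clinic only | Both strata | Neither ÷ clinic | Neither ÷ both |
|---|---|---|---|---|---|
| 0 | 0.177 | 0.177 | 0.150 | 1.00 | 1.18 |
| 0.05 | 0.187 | 0.179 | 0.150 | 1.04 | 1.25 |
| 0.10 | 0.197 | 0.181 | 0.152 | 1.09 | 1.30 |
| 0.17 | 0.207 | 0.180 | 0.152 | 1.15 | 1.36 |
| 0.37 | 0.237 | 0.179 | 0.152 | 1.32 | 1.56 |

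Leaving clinic out gains nothing when clinic variance is zero and widens the SE otherwise. The clinic loss lies in the reported SE: at clinic variance 0.10 the actual spread of the estimates is 0.167 with or without clinic, while the reported SE is 0.197 without it. With both strata, the SE (0.152) and the spread (0.154) agree.

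**Step 4. Dependence on the unknown correlation** (clinic variance 0.10, 4 clinics). Unadjusted ÷ adjusted for both strata: 0.196/0.171 = 1.15 at correlation 0.4, 1.30 at 0.7, and 0.196/0.136 = 1.44 at 0.85.

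**Step 5. Size of the estimand change.** The ratio of clinic-conditional to population-averaged log odds ratio is about √(1 + 0.346 × clinic variance). At 0.05 it is 1.009 and at 0.37 it is 1.062. A conditional odds ratio of 1.50 corresponds to a marginal one of 1.49 to 1.46.

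**The case against.** Several points on the other side are fair.

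- *Fixed-effects need not mean that clinic is left out.* It could mean clinic indicators, as in H2. Since the test compares models with and without clinic random effects, a model without clinic is the natural reading, but not the only one. If indicators were meant, the SE loss from omitting clinic falls away and the text needs clarifying. The selection test would still be weak and its threshold undefined.
- *Random-effects models do have a likelihood.* A reader might infer that the plan runs an invalid test on the weighted, replicated GEE data. The article does not say so. What it leaves unclear is which model the test belongs to and how its result carries over to the GEE.
- *A covariate list can be left to an SAP.* A reader might infer that baseline use has been excluded from H1/H3. The text is only silent, and silence alone would be no finding. The point rests on the stated selection rule; baseline use enters because a replacement model has to be written anyway and this is the other randomization stratum.
- *The precision gains rest on assumptions.* This stands. A reader might convert the SE ratios into an equivalent number of extra providers. The documents do not support that: no baseline-to-follow-up correlation is given, and stratified randomization already balances both factors.

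**Conclusion.** The selection rule should go. With about 3–5 clinics it misses a clinic variance of 0.05–0.17 in roughly 37–82% of trials when provider variation is modelled. When it is not, the rule signals absent clinic variation in 63–87%. The stated power rationale fails: leaving clinic out gains nothing at zero clinic variance and widens the SE by about 4–15% at variances of 0.05–0.17.

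The damage is limited. A reader might infer bias or an inflated false-positive rate; stratified randomization balances the strata, and what is shown is an overstated SE, hence lost precision. A reader might also make much of the switch between a marginal and a clinic-conditional odds ratio; the difference is real but only about 1–6% on the log odds ratio.

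The size of the precision loss rests on the assumed variances, on the first-stage comparison standing in for the full SMART analysis, and on reading the fixed-effects branch as a model without clinic. The trial is not invalidated, but the change is worth making because it is nearly free.

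**What to change.** Delete the test-and-switch rule in Data analysis, Aim 1, and pre-specify one model for all H1/H3 contrasts:

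- A weighted GEE clustered on provider, with robust Wald tests as now planned.
- Clinic indicators (2–4 df) and the provider's six-month pre-randomization interpreter use as a continuous covariate (1 df), kept whatever their significance.
- The resulting odds ratio reported as covariate-adjusted. A logistic GEE coefficient with these covariates is conditional on clinic and baseline use, so if a marginal odds ratio is wanted it must be obtained by standardization.
- Clinic variation reported descriptively, or through a random-effects model as a sensitivity analysis only.

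The cost is one paragraph of analysis text and 3–5 model degrees of freedom. Both covariates are already collected for the randomization.

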**Implementation and effectiveness outcomes**								
Interpreter use (primary outcome)	*Dichotomous variable* per non-English language patient visit, constructed by matching professional interpreter vendor invoices to clinic visits with enrolled providers; calculated overall and as assigned (e.g., mobile video interpreting for assigned providers) [27, 46, 57]							X
Patient/parent comprehension	*Dichotomous variable* coded as yes vs no or unclear, based on 2 blinded coders evaluating concordance between patient-reported and provider-documented diagnosis, against the standard of whether a follow-up provider would know the diagnosis based on the patient-reported information [46, 70]			X			X	

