**Patient factors**								
Patient/parent health literacy	Confidence in filling out medical forms, with options from extremely confident (0) to not at all confident (4); scores ≥ 2 considered low health literacy [71–73]			X				
Visit type	Annual/wellness exam, acute visit, or chronic condition follow-up						X	X
Patient demographics	*-Insurance:* None/public insurance, private insurance *-Race/ethnicity:* American Indian or Alaska Native, Asian, Black, Hispanic, Native Hawaiian or Pacific Islander, multiracial/other, White, prefer to self-describe *-Sex*: Male, female, or self-describe *-Age*: Continuous variable			X				X
Respondent demographics (patient or parent)	*-English proficiency*: Very well, well, not well, not at all *-Education*: < high school, high school graduate, > high school *-Respondent relationship to patient*: Self, mother, father, other guardian			X				
**Provider and clinic barriers, organized by Theoretical Domain Framework and COM-B categories** [37]								

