#### Patients

We will enroll 3 populations of adult patients or parents of pediatric patients (henceforth “patients”) who use a language other than English, all being seen by enrolled providers. For our *administrative population*, we will include administrative data from all patients who were recorded as using a language other than English in the medical record and were seen by enrolled providers, for the interpreter use outcome. For our *survey population*, we will enroll patients who prefer medical care in the four most common non-English languages across clinics, who are in clinic for an acute concern (e.g., sore throat, new ankle pain). These individuals will be invited to complete a survey (*n* = 648), and a subset will be invited to complete a 20–30 min qualitative interview (*n* = 75). We will also recruit patients for our *video-recording population* (*n* = 100). Patients who use a language other than English with any visit type who consent will be eligible for video recording.

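### The H2 comprehension model pools its named covariates by provider and does not name three respondent traits that the same survey collects: health literacy, education and English proficiency.

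*Protocol article*

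**What the plan says.** The H2 paragraph under Data analysis, Aim 1 fixes the level of the model: "A weighted GEE logistic regression model predicting patient/parent comprehension at the visit level will be estimated". It then lists the adjustment set: "Baseline covariates will include the clinic, patient demographics (age, sex, language), and patient comorbid conditions", followed by the phrase "pooled at the provider level".

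Table 1 defines the outcome through "concordance between patient-reported and provider-documented diagnosis", so it belongs to the person who answers the survey. Under Patient factors, Table 1 keeps two groups of demographics apart. Age and sex are listed for the patient. English proficiency (four levels), education (three levels) and relationship to the patient are listed for the respondent. Health literacy has its own row for the patient or parent, scored 0 to 4, with 2 or more counted as low. Health literacy and the respondent traits come from the patient survey.

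The Patients section uses the word patients for "adult patients or parents of pediatric patients". The opening of Data analysis relies on randomization against unobserved confounders and plans multiple imputation as a sensitivity analysis for missing comprehension data. It does not list the imputation variables.

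**The concern.** Whether someone can report a diagnosis after a visit held across a language barrier plausibly depends on that person's health literacy, schooling and English. These vary from respondent to respondent. The plan collects all three and then names an adjustment set that contains none of them. It also reduces the named set to provider level, where it cannot account for differences between respondents of the same provider.

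Providers are randomized; respondents are not. They are invited and surveyed after their provider's assignment, and the H2 sample consists only of those who complete the survey. Balance among respondents is therefore less secure than balance among providers. At stake are some precision and some protection for a secondary outcome.

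**Working it through.** **1. Inputs.** The section on patient/parent comprehension gives 216 surveys per group (648 in total), a 14-point difference and power of at least 80%. The section on interpreter use allows for the loss of up to 9 of 55 providers, so 55 − 9 = 46 remain and 648/46 ≈ 14.1 surveys per provider. The significance level and the baseline comprehension rate are not stated. I assume two-sided 0.05, independent surveys and baseline rates from 0.30 to 0.80.

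**2. The plan's own figure.** Power = Φ{[Δ√n − 1.96√(2p̄(1−p̄))] / √(p₁(1−p₁)+p₂(1−p₂))}. The worst case is 0.43 versus 0.57:

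- 0.14 × √216 = 2.058
- 1.96 × √0.5 = 1.386
- √0.4902 = 0.700
- (2.058 − 1.386)/0.700 ≈ 0.96, so power = 83.1%

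At 0.80 versus 0.94 power is 99.2%. The stated figure reproduces under independence.

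**3. Levels side by side.**

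| Item | Level |
|---|---|
| Comprehension (H2 outcome) | one respondent, one visit |
| Clinic, age, sex, language, comorbid conditions | pooled by provider |
| Health literacy, education, English proficiency | each respondent; not named for H2 |

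If a trait has an intraclass correlation within provider of 0.02 to 0.10 (assumed), then 90% to 98% of its variance lies between respondents of the same provider. No provider-level covariate can reach that part.

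**4. Precision (illustration).** If the three traits explained a share R² of outcome variance, the effective n per group would be about 216/(1 − R²). At 0.43 versus 0.57:

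| R² (assumed) | effective n | power |
|---|---|---|
| 0 | 216 | 83.1% |
| 2% | 220 | 83.9% |
| 5% | 227 | 85.0% |
| 10% | 240 | 86.8% |
| 15% | 254 | 88.6% |

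This is a linear-model approximation. In logistic regression the gain comes mainly through a larger conditional log odds ratio rather than a smaller standard error.

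**5. Chance imbalance in one trait.** The SD of the difference in trait prevalence between two groups is √(2π(1−π)·DE/216), with DE = 1 + (14.1 − 1)·ICC. The shift in the comprehension difference is that imbalance times the trait's effect.

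- Low end (π = 0.3, ICC = 0.02, effect 10 points): DE = 1.262, SD = 5.0 points, 95% shift ±1.96 × 5.0 × 0.10 ≈ ±1.0 point.
- High end (π = 0.5, ICC = 0.10, effect 20 points): DE = 2.309, SD = 7.3 points, 95% shift ±1.96 × 7.3 × 0.20 ≈ ±2.9 points.

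**6. Simulation (illustration).** Set-up: 46 providers with 14 surveys each, two arms, exchangeable GEE, treatment log odds ratio 0.6, trait log odds −0.5 to −1.0, and panels varying with SD 0.4 to 1.0 on the logit scale. Power without/with the three traits was:

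- 600 runs per setting: 0.85/0.87, 0.86/0.91, 0.85/0.87, 0.79/0.84, 0.80/0.88.
- A second set, 400 runs per setting: 0.87/0.87, 0.83/0.87, 0.85/0.91, 0.80/0.85, 0.74/0.88.

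Monte Carlo error is about √(0.85 × 0.15/600) = 1.5 points and √(0.85 × 0.15/400) = 1.8 points for each estimate. The comparator adjusted for age and sex only. It did not reproduce clinic, language, comorbidity, the pooling or the three groups, so these figures show direction and rough size, not the plan's actual power.

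**The case against.** The strongest reply is that covariate choice is largely a matter of preference in a randomized comparison. Assignment is stratified by clinic and baseline interpreter use, leaving out a prognostic covariate does not by itself bias H2, and chance imbalance is already in the standard error. The article is condensed, and its list says what will be included, not that nothing else will be. The imputation draws on observed data, which permits these variables. All of that stands, and it limits the point to a modest one. It does not remove it: the article does name a specific set and a level for it, and neither uses what the survey measures on the respondent.

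Four stronger readings are tempting, and the documents do not support them.

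- *The model adjusts for the wrong person at pediatric visits.* Table 1 lists age and sex for the patient, but the Patients section extends that word to parents. This is an ambiguity confined to pediatric visits, whose share is not given.
- *Comorbid conditions have no source and should go.* They have no row in Table 1, but the study uses medical-record and administrative data. Language is also missing from the Table 1 demographics row, although the Patients section says it is recorded. An acute visit does not make comorbidity irrelevant either.
- *Adjustment would cure dilution from respondents who speak English very well.* A main-effect term does not do that.
- *The H2 power claim is wrong.* It reproduces.

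The timing objection also stands in part. The plan speaks of baseline covariates, and these traits are self-reported after the visit.

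**Conclusion.** The point holds as an improvement to the analysis, not as an error in a stated figure. The H2 model is at visit level, its named covariates are pooled by provider, and three respondent traits already collected are not named. If the pooling phrase was meant for comorbid conditions alone, the three traits are still unnamed.

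The gain in power runs from nil, in the weakest setting tried, to several points in most others (14 in one simulated setting). The shift from imbalance in one trait is about 1 to 3 points, against the 14-point target. Both ranges rest on assumed prevalences, trait strengths and intraclass correlations, none of which the documents give. Nothing in the documents shows that respondents will in fact differ between groups. The argument is that provider randomization alone does not guarantee that they will not.

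**What to change.** In the H2 paragraph of Data analysis, Aim 1:

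- Add respondent health literacy (the 0–4 score or the stated cut-off of 2), education and English proficiency as individual-level covariates.
- Name the same variables in the multiple imputation of comprehension.
- State whose age and sex are used at pediatric visits.
- Keep comorbid conditions if a data source is available, and name that source.

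The cost is a sentence or two and no new data, but the set should be settled before outcome data are seen. There are two downsides. The odds ratio becomes conditional on the added traits, so its value and meaning change. The traits are recorded after the visit; education is safe from influence by the visit and English proficiency nearly so, but confidence in filling out forms is the least certain.
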